#### 5.2.3 Secondary Outcome Analyses

For secondary analyses, the following statistical methods will be used:

1. **Continuous Variables**: Analyzed using Kruskal-Wallis tests (due to anticipated non-normal distributions) for three-way comparisons among AI-alone, AI-assisted, and physician-only groups. For direct comparison between AI-assisted and physician-only groups, Mann-Whitney U tests will be used.
2. **Categorical Variables**: Compared using chi-square or Fisher's exact tests as appropriate based on expected cell counts.
3. **Interrater Reliability**: Assessed using Fleiss' kappa for multiple raters (for the three independent evaluators scoring report quality) and Cohen's kappa for assessing agreement between AI and AI-Physician groups.
4. **Report Characteristics**:
   - Word count will be compared between groups using non-parametric tests
   - Number of recommendations included in reports will be compared between groups
   - Number of non-relevant recommendations will be quantified and compared
5. **Physician Satisfaction**: Analyzed using descriptive statistics for Likert scale responses (mean, standard deviation) and thematic analysis for free-text comments.

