**2. Introduction**

**2.1 Background and Rationale**

**2.1.1 Intended Use of the AI Intervention**

The INSPIRE AI framework is intended to assist neurologists in interpreting electrodiagnostic (EDX) tests (including electromyography and nerve conduction studies) and generating diagnostic reports. The primary purpose is to reduce documentation burden, standardize reporting, and potentially improve diagnostic accuracy. The intended users are board-certified neurologists who regularly perform EDX tests in clinical practice.

Within the clinical pathway, EDX studies are conducted to evaluate patients with suspected neuromuscular disorders. Currently, physicians manually interpret the raw data and compose reports, a process that is time-consuming and subject to variation in quality and completeness. The INSPIRE system will generate a preliminary report based on the raw EDX data, which will then be reviewed, verified, and edited by a neurologist before finalization. This is expected to streamline workflow while maintaining or improving diagnostic accuracy.

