**2.4 Trial Design**

This is a single-center, randomized controlled trial with two parallel arms and 1:1 allocation ratio:

1. Intervention arm: AI-assisted physician EDX report generation
2. Control arm: Standard physician-only EDX report generation

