### 5.2 Statistical Methods

#### 5.2.1 Sample Size

The study will enroll 200 participants (100 per arm) during the one-month study period at the neuromuscular outpatient clinic at Rambam Healthcare Campus. While we acknowledge that this sample size may be insufficient to detect small differences between groups, it will provide initial insights into the performance differences between AI-assisted and physician-only approaches and inform future larger studies if results suggest potential benefits.

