#### 5.2.2 Primary Outcome Analysis

The primary analysis will compare the AIGERS scores between the AI-assisted physician group and the physician-only group. We will first check for normality using the Shapiro-Wilk test. If data are not normally distributed, which is anticipated based on similar metrics, we will use the non-parametric Kruskal-Wallis test for the primary comparison. A two-sided p-value <0.05 will be considered statistically significant.

In addition to the main comparison between intervention and control groups, we will also evaluate the AI-alone performance by comparing the AI-generated reports (before physician modification) with both the AI-assisted physician and physician-only groups using the same statistical approach.

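### AI-alone and AI-assisted reports come from the same patients but are compared by Kruskal-Wallis as independent groups, which makes these additional and secondary tests conservative

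*Protocol*

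**What the plan says.** Protocol section 2.4 describes a "randomized controlled trial with two parallel arms and 1:1 allocation ratio": AI-assisted reporting and physician-only reporting. Section 5.2.1 sets the size: "The study will enroll 200 participants (100 per arm) during the one-month study period".

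In the AI arm, section 2.1.1 says that INSPIRE produces a preliminary report, "which will then be reviewed, verified, and edited by a neurologist before finalization". Section 3.3.4 gives the same order of steps.

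Section 5.2.2 names Kruskal-Wallis for the primary comparison if scores are not normal, which the protocol expects. It then adds an evaluation of the AI by itself, "comparing the AI-generated reports (before physician modification) with both the AI-assisted physician and physician-only groups using the same statistical approach". Section 5.2.3 specifies Kruskal-Wallis for continuous variables "for three-way comparisons among AI-alone, AI-assisted, and physician-only groups", and continues: "For direct comparison between AI-assisted and physician-only groups, Mann-Whitney U tests will be used".

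No paired or clustered method is named for these scores. Yet section 5.2.3 also plans Cohen's kappa between the AI and AI-physician reports, and that statistic needs both readings on the same cases.

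**The concern.** AI-alone is not a third set of patients. By the definition in section 5.2.2 it is the state of the AI-arm reports before editing, so each draft score has a partner: the score of the final report on the same patient and the same EDX data. Kruskal-Wallis assumes independent samples. It measures the difference between draft and final against the full between-patient spread, although most of that spread cancels within a pair.

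What is at stake is the contrast between AI-alone and AI-assisted. It is the only comparison in the plan that shows what physician review adds to the draft, and the intended use in section 2.1.1 rests on that review. A test that is biased towards no difference could miss a real effect of editing, and the result could then be read as evidence that review changes little.

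**Working it through.** **Inputs from the protocol.** 100 patients per arm (section 5.2.1). Two-sided 5% level: "A two-sided p-value <0.05 will be considered statistically significant" (section 5.2.2). AI-alone and AI-assisted therefore give 100 pairs, and physician-only gives 100 separate patients. The protocol states no effect size, SD or power, so it has no figure to reproduce.

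**Assumptions.** Correlation rho between draft and final score: 0.3 to 0.9. Differences: 0.2 to 0.4 SD. Scores are normal with equal variance. Drafts exist only in the AI arm.

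**Type I error of an unpaired test on paired data.** With n pairs and unit SD, the unpaired test uses variance 2/n for the difference, while the true variance is 2(1 − rho)/n. The true size is therefore

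2 × [1 − Φ(1.96 / √(1 − rho))]

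- rho 0.3: 1.96/√0.7 = 2.34, size 0.019
- rho 0.5: 1.96/√0.5 = 2.77, size 0.0056
- rho 0.7: 1.96/√0.3 = 3.58, size 0.0003

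Simulation of the rank tests (10,000 null runs, n = 100 per group) agrees:

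| Test | rho 0.3 | rho 0.5 | rho 0.7 | rho 0.9 |
|---|---|---|---|---|
| Kruskal-Wallis, AI-alone v AI-assisted | 0.019 | 0.006 | 0.001 | 0.000 |
| Signed-rank, AI-alone v AI-assisted | 0.049 | 0.047 | 0.047 | 0.053 |
| Kruskal-Wallis, three groups | 0.041 | 0.033 | 0.032 | 0.036 |
| Mann-Whitney, AI-assisted v physician-only | 0.050 | 0.050 | 0.047 | 0.050 |
| Mann-Whitney, AI-alone v physician-only | 0.051 | 0.049 | 0.051 | 0.050 |

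The two tests that use the pair as if it were independent fall below 5%. Both contrasts with physician-only keep their level, because they compare different patients.

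**Power for AI-alone v AI-assisted, unpaired rank test v signed-rank (simulated):**

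| Difference | rho 0.5 | rho 0.7 | rho 0.9 |
|---|---|---|---|
| 0.2 SD | 0.21 v 0.49 | 0.15 v 0.71 | 0.06 v 0.99 |
| 0.25 SD | 0.35 v 0.66 | 0.35 v 0.88 | 0.26 v 1.00 |
| 0.3 SD | 0.56 v 0.84 | 0.58 v 0.97 | 0.64 v 1.00 |
| 0.4 SD | 0.87 v 0.97 | 0.91 v 1.00 | 0.99 v 1.00 |

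Normal-theory check at 0.25 SD and rho 0.5. The standard error of the paired difference is √(2 × 0.5/100) = 0.10, and the unpaired test rejects beyond 1.96 × √(2/100) = 0.277.

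- Unpaired: Φ((0.25 − 0.277)/0.10) = Φ(−0.27) = 0.39
- Paired: Φ(0.25/0.10 − 1.96) = Φ(0.54) = 0.71

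The rank tests lie a little below these values, as expected.

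**Power of the three-way test.** If only physician-only differs, by 0.4 SD, power falls from 0.82 at rho 0 to 0.77 at rho 0.5 and 0.75 at rho 0.9.

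**The case against.** The strongest reply is that little depends on this. Section 5.2.2 presents the AI-alone evaluation as an addition to the main comparison, and section 5.2.3 is secondary. With positive correlation the error is conservative, so it creates no false benefit. Section 5.2.1 already concedes that small differences may be missed. All of this stands, and it limits the severity. It does not make the test right: the protocol names the method, so this is not a detail left to a statistical analysis plan.

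The figures are also illustrative. AIGERS is bounded between 0 and 1 and expected to be non-normal, and drafts signed without edits would give zero differences. That would shift the numbers but not the direction of the error.

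A reader might infer more than the protocol supports:

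- *That the main result is invalid.* It is not. The primary comparison is between two randomised arms, and Kruskal-Wallis on two groups is equivalent to a two-sided Mann-Whitney test.
- *That the planned Mann-Whitney test is wrong.* Section 5.2.3 assigns it only to AI-assisted against physician-only, where its size is about 5%.
- *That most of the power is lost.* This is true of one contrast only, for small differences with substantial correlation. At 0.25 SD and rho 0.5 the loss is just under half; at 0.4 SD it is 0.01 to 0.10.
- *That assessors will be unblinded by meeting AI-arm cases twice.* Sections 3.4.1 and 4.2 name three blinded assessors but do not say whether they also score drafts, or in what order. This is a possible risk, not a documented one.

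**Conclusion.** Wrong as written, in additional and secondary analyses only. It should be fixed, but no primary conclusion depends on it. The drafts and the final AI-arm reports are matched by patient, and the named test treats them as independent.

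The AI-alone against AI-assisted test is strongly conservative and can miss a real but small effect of physician editing. The three-way test is only mildly conservative. How much is lost cannot be fixed from the protocol, because it gives neither a correlation nor an effect size; the tables above show the range. A draft and its edited version should correlate strongly, so the higher values of rho are plausible. The conclusion that AI-alone against physician-only keeps its level rests on drafts existing only in the AI arm, as the definition in section 5.2.2 implies.

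**What to change.** In sections 5.2.2 and 5.2.3:

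1. Analyse AI-alone against AI-assisted with a Wilcoxon signed-rank test on within-patient differences. State how zero differences from unedited drafts are handled, and report an estimate of the difference with a 95% CI.
2. Keep two-sample rank tests for AI-assisted and for AI-alone against physician-only.
3. Drop the three-way Kruskal-Wallis test, or replace it with a model clustered by patient (mixed or GEE).
4. If the same blinded assessors also score the drafts, lock the scores of all 200 final reports before any draft is released to them, because a case seen twice could reveal the arm.

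Items 1 to 3 are changes of wording and need no further patients or data. Item 4 costs only the order of scoring. Running INSPIRE on control-arm cases, so that AI-alone against physician-only also becomes paired, would be an optional extension and is not needed to correct the error.

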**3.4 Outcomes**

**3.4.1 Primary Outcome**

The primary outcome is the quality of EDX reports as measured by the AI-Generated EMG Report Score (AIGERS). This composite score (range 0-1) evaluates report quality based on:

1. Finding Score (50%): Accuracy and completeness of reported EDX findings
2. Clinical Diagnosis Score (50%): Accuracy and appropriateness of the clinical interpretation

The AIGERS score will be independently assessed by three board-certified neurologists who are not involved in the report generation and are blinded to the study arm.

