**3.4.2 Secondary Outcomes**

1. Word count and comprehensiveness of reports
2. Physician satisfaction with the AI tool (5-point Likert scale survey)
3. Number of recommendations included in reports
4. Technical performance metrics for the AI system (sensitivity, specificity for detecting abnormal studies)
5. Inter-rater reliability of reports assessed by kappa scores

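### Fleiss' kappa is assigned to a graded 0-1 quality score and would understate rater agreement, severely if AIGERS is finely graded

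*Protocol*

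**What the plan says.** Section 3.4.1 defines what is rated: "The primary outcome is the quality of EDX reports as measured by the AI-Generated EMG Report Score (AIGERS"). It continues "This composite score (range 0-1) evaluates report quality" and gives two equally weighted parts: "Finding Score (50%): Accuracy and completeness of reported EDX findings" and "Clinical Diagnosis Score (50%): Accuracy and appropriateness of the clinical interpretation". Three neurologists, blinded to arm, score each report independently.

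Item 5 of section 3.4.2 makes agreement a secondary outcome: "Inter-rater reliability of reports assessed by kappa scores". Section 5.2.3 then names the statistics. For the three evaluators it is Fleiss' "kappa for multiple raters (for the three independent evaluators scoring report quality"). Under the same interrater-reliability item it adds Cohen's "kappa for assessing agreement between AI and AI-Physician groups".

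Elsewhere the protocol handles AIGERS as a continuous score. Section 5.2.2 plans a normality check and a rank test, and section 5.2.4 places AIGERS among measurements it calls continuous. The protocol gives no cut-points, categories, weights or ICC.

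**The concern.** Fleiss' kappa was built for nominal categories. It asks only whether raters chose the identical category and ignores order and distance. On a graded score, raters who differ by a trivial amount are counted as disagreeing completely, and this happens more often as the scale gets finer.

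The primary outcome rests on human judgement, and item 5 is the planned quantitative check that the judgements are reproducible. A low kappa obtained this way could not be told apart from real disagreement and could discredit a sound endpoint.

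A smaller matter sits beside it. By sections 2.1.1 and 3.3.4, the AI-physician report is the AI draft after the physician has reviewed and edited it. A kappa between the two compares a text with its own revision. That is not agreement between independent raters, although it is listed under interrater reliability.

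**Working it through.** The protocol gives no kappa, ICC or target, so there is no figure to reproduce.

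**Inputs from the protocol.** Three raters (3.4.1); score range 0-1 with two 50% components (3.4.1); 200 reports (5.2.1); Fleiss' kappa with no weighting stated (5.2.3).

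**Assumptions, because the protocol is silent.** Mean and SD of AIGERS, true single-rater reliability, and number of score levels.

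**Formulas.** For report i, with n_ij of the 3 raters choosing value j:

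- P_i = Σ_j n_ij(n_ij − 1) / (3 × 2)
- P_e = Σ_j p_j², where p_j is the overall share of value j
- Fleiss' kappa = (mean P_i − P_e) / (1 − P_e)
- ICC(2,1) = (MSR − MSE) / [MSR + (k − 1)MSE + k(MSC − MSE)/n], two-way random effects, absolute agreement, with k raters and n reports

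**A case that can be checked by hand.** Let the middle rater's score be uniform over 17 values in 0.05 steps, from 0.10 to 0.90. One rater is always a step below and one always a step above.

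- No two raters ever match, so mean P_i = 0.
- Ratings cover 19 values with shares 1/51, 2/51, then fifteen of 3/51, then 2/51, 1/51. P_e = (1 + 4 + 15 × 9 + 4 + 1)/2601 = 145/2601 = 0.056.
- Kappa = −0.056/0.944 = −0.06.
- In step units the variance between reports is (17² − 1)/12 = 24, the variance between raters is 1, and there is no residual. ICC = 24/(24 + 1) = 0.96.

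A simulated sample of 200 such reports gave −0.06 and 0.96.

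**Simulation.** Rating = true quality + rater error, with mean 0.7 and SD 0.15, clipped to 0-1 and rounded to the step; 200 reports, 3 raters. Repeat runs agree to about 0.01.

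| Step | Kappa, true ICC 0.80 | ICC on same ratings | Kappa, true ICC 0.90 | ICC on same ratings |
|---|---|---|---|---|
| 0.01 | 0.03 | 0.80 | 0.05 | 0.90 |
| 0.05 | 0.13 | 0.79 | 0.22 | 0.89 |
| 0.1 | 0.26 | 0.77 | 0.40 | 0.87 |
| 0.25 | 0.49 | 0.66 | 0.63 | 0.76 |
| 0.5 | 0.58 | 0.59 | 0.70 | 0.70 |

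**Sensitivity to the assumed distribution.** With mean 0.6, SD 0.2 and reliability 0.90, kappa is 0.04, 0.17, 0.32, 0.58 and 0.66 for 101, 21, 11, 5 and 3 levels. The ICC is 0.90, 0.89, 0.88, 0.80 and 0.70. At 21 levels, an SD of 0.1 gives 0.31 against 0.88, and an SD of 0.3 gives 0.17 against 0.89. Rating 300 reports, as when 100 unedited AI drafts are scored too, changes these results by no more than 0.01.

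**Effect of averaging two components.** Two components with L equally spaced levels each give a total with 2L − 1 possible values. With reliability 0.90 and SD 0.3 per component, two 5-level components (9 totals) give kappa 0.34 against ICC 0.84. Two 3-level components (5 totals) give 0.51 against 0.75. A total with only three values, where the gap closes, would need each component to be scored 0 or 1.

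**Weighted kappa.** In the mean-0.6, SD-0.2 runs, the mean pairwise quadratic-weighted kappa lies within about 0.002 of the ICC, so the shortfall comes from ignoring distance.

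**The case against.** **Granularity is not stated.** A reader might infer that good agreement is bound to be reported as poor. The protocol does not support that. It gives a range and two weights, and section 5.1.1 mentions standardized scoring forms without showing their items. On a coarse scale the understatement is moderate or absent. This objection stands, and the size has to be given as a range.

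**Kappa may be meant for a categorical item.** Section 5.2.3 does not use the name AIGERS, and categories and weights are details an analysis plan could supply. This stands only in part. The statistic is tied to evaluators scoring report quality, which section 3.4.1 defines as AIGERS, and no other rating by these three evaluators is named. If another was meant, the protocol gives AIGERS itself no agreement statistic.

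**Kappa still responds to agreement.** It would be wrong to say it reflects granularity and not agreement. At 0.05 steps it rises from 0.13 to 0.22 as true ICC goes from 0.80 to 0.90. It depends on both, so a single value cannot be interpreted without knowing the scale.

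**Other safeguards exist.** The raters are independent and blinded, reports are reformatted to one template (4.2), and section 3.3.1 reports that AIGERS separated two systems. Rater agreement is therefore not the only support for the endpoint.

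**The AI versus AI-physician kappa is a small matter.** A reader might infer that it will pass for AI accuracy. The protocol calls it agreement, gives accuracy its own outcome (sensitivity and specificity, 3.4.2 item 4), and logs whether physicians corrected AI errors (6.3). High agreement is also not guaranteed, since a physician may rewrite the draft. Only the label is at fault.

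**Limited consequence.** Agreement is the last of five secondary outcomes, and no stated decision depends on it. This stands.

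**Conclusion.** The concern holds in a conditional form. The protocol assigns a nominal-category statistic to a score that it treats as continuous, and the resulting figure would understate rater agreement. With 0.1 steps or finer, an assumed mean of 0.7, SD of 0.15 and true ICC of 0.80, kappa would be about 0.03 to 0.26 where the ICC on the same ratings is about 0.77 to 0.80. At 0.25 steps the shortfall is moderate (0.49 against 0.66), and at 0.5 steps it is negligible. The number of levels, mean, SD and true reliability are all assumptions. The direction held in every graded setting examined, but the size did not.

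A reader might go on to doubt the primary comparison. Nothing supports that: the between-arm test does not use kappa. The damage is confined to secondary outcome 5 and to what it is taken to say about the primary outcome's ratings. It should be corrected, but it does not threaten the trial's main result.

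**What to change.** - In section 5.2.3, replace Fleiss' kappa for report quality with a two-way random-effects, absolute-agreement ICC. Report it for a single rater and for the mean of three, with 95% CIs, for total AIGERS and for each of its two components.
- If a component has only a few ordered levels, use a weighted kappa for it and state the weights.
- Keep Fleiss' kappa only for nominal ratings, such as normal versus abnormal, and name the rating.
- State how many values AIGERS and its components can take.
- Amend item 5 of section 3.4.2 so that it no longer limits agreement to kappa.
- Move the AI versus AI-physician kappa out of interrater reliability, label it as acceptance of the AI draft, and name the classification compared.

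The cost is analysis wording only. The ICC uses the same three independent scores per report, so no new data or rating time is needed, and the primary analysis does not change.

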#### 5.2.4 Data Distribution and Transformation

Based on prior experience with similar metrics, we anticipate that the AIGERS scores and other continuous measurements may not be normally distributed. We will apply appropriate transformations if necessary to achieve normality. If transformations are unsuccessful, non-parametric tests will be used as the primary analytical approach.

#### 5.2.5 Handling of Missing Data

Missing data will be addressed as follows:

1. Cases where EDX data quality is insufficient for AI analysis will be documented as technical failures
2. For the primary outcome analysis, we will use complete case analysis if missing data is <5%
3. If missing data exceeds 5%, multiple imputation techniques will be employed
4. Sensitivity analyses will be conducted to assess the impact of missing data on outcomes

#### 5.2.6 Subgroup and Exploratory Analyses

1. **Diagnostic Category Subgroups**: Separate analyses for common diagnostic categories (radiculopathy, mononeuropathy, polyneuropathy) if sufficient numbers are available in each subgroup.
2. **Normal vs. Abnormal Studies**: Stratified analysis comparing AI performance on normal versus abnormal EDX studies.
3. **Physician Experience**: Exploratory analysis of whether physician experience level modifies the effect of AI assistance.
4. **Error Pattern Analysis**: Detailed categorization and analysis of error types made by AI versus physicians.

All secondary and exploratory analyses will be clearly identified as such in reporting, and appropriate corrections for multiple testing will be applied when interpreting results.

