**3.3.2 Input Data Acquisition and Selection**

The input data for the AI intervention will consist of:

1. Patient demographic information (age, sex, clinical indication)
2. Medical history relevant to neuromuscular outpatient clinic
3. Complete nerve conduction study data (tables of measurements)
4. Needle EMG recordings (quantitative and qualitative descriptions)
5. Visual representations of waveforms

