**3.5 Participant Timeline**

The study will follow a simple timeline:

1. Screening and enrollment prior to scheduled EDX appointment
2. Randomization on the day of the EDX study
3. EDX testing performed according to standard clinical protocols
4. Report generation (either AI-assisted or physician-only)
5. Quality assessment and data collection
6. No follow-up visits required for the study (though patients may have clinical follow-up as determined by their treating physician)

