**4.1.2 Concealment Mechanism**

Allocation will be concealed using sequentially numbered, opaque, sealed envelopes that will be opened only after the participant has been enrolled and immediately before the EDX study begins.

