**4.2 Blinding**

Due to the nature of the intervention, the neurologists generating the reports cannot be blinded to the study arm. However, the three neurologists assessing the quality of the reports (outcome assessors) will be blinded to the method of report generation. Reports from both arms will be reformatted to a standard template to prevent identification of the study arm based on formatting or style.

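### The diagnostic subgroups have no stated source that is independent of the scored report, and analysing them separately does not test whether the AI effect differs between them

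*Protocol*

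**What the plan says.** Protocol section 5.2.6 lists, as its first subgroup analysis: "Separate analyses for common diagnostic categories (radiculopathy, mononeuropathy, polyneuropathy", on condition that each subgroup is large enough. Its second item is "Stratified analysis comparing AI performance on normal versus abnormal EDX studies". Neither item says who assigns the label, when, or from what material. The item on physician experience in the same section asks whether experience modifies the AI effect; the diagnostic item has no such wording. The section treats secondary and exploratory analyses as needing to be identified as such, and it promises a correction for multiple testing without naming one.

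Four other places bear on the point:

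- **Outcome.** Section 3.4.1 makes this half of AIGERS: "Clinical Diagnosis Score (50%): Accuracy and appropriateness of the clinical interpretation".
- **Timing.** Section 3.5 places "Randomization on the day of the EDX study", ahead of testing and reporting. Section 4.1.2 has the envelope "opened only after the participant has been enrolled and immediately before the EDX study begins".
- **Blinding.** Under section 4.2, "the neurologists generating the reports cannot be blinded to the study arm".
- **Referral information.** Section 3.3.2 includes in the AI input data "Patient demographic information (age, sex, clinical indication", and section 3.2.1 admits patients by referral.

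Secondary objective 4 (section 2.3) is to find the areas of EDX reporting in which AI help brings the most benefit.

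**The concern.** Radiculopathy, mononeuropathy and polyneuropathy are conclusions of the work-up. In this trial the conclusion is written under the arm's own method and is itself scored. If that conclusion also decides the subgroup, a wrong diagnosis both lowers the score and can move the patient to another subgroup. The two arms' polyneuropathy groups, say, would then no longer be comparable samples of patients, and the protection of randomisation would be lost inside the subgroup.

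The second issue is separate. A set of within-category comparisons answers whether there is an effect in each category. It does not answer whether the effect is larger in one category than in another. A significant result in one category beside a non-significant result in the next is not evidence of a difference. What is at stake is any statement about where AI assistance helps most; the overall comparison of the arms is not at stake.

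**Working it through.** The protocol gives no effect size, SD or subgroup size, so there is no figure of its own to reproduce. The check has three parts.

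**1. Order of events and sources of a label.** Enrolment, then envelope, then EDX study, then report (sections 3.5 and 4.1.2). Any EDX diagnosis is therefore post-randomisation. The only diagnosis the protocol describes being produced is the one in a report. Three places presuppose some view of the right answer: the assessors' rating of diagnostic accuracy (3.4.1), AI sensitivity and specificity (3.4.2) and the log of misclassifications (6.3). None defines a reference diagnosis or links one to the subgroups.

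**2. Size of the bias if the label comes from the report.** All inputs here are assumptions.

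*Illustration A, in SD units, no true effect.* Of all patients, 25% are clear polyneuropathy. A further 15% are borderline and score 1 SD lower whatever their label. Borderline cases are labelled polyneuropathy in 60% of AI-arm reports and 30% of control reports.

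- Borderline share of the AI-arm subgroup: 0.15 × 0.6 / (0.25 + 0.15 × 0.6) = 0.09 / 0.34 = 0.265
- Borderline share of the control subgroup: 0.15 × 0.3 / (0.25 + 0.15 × 0.3) = 0.045 / 0.295 = 0.153
- Spurious difference: −0.265 + 0.153 = −0.11 SD

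*Illustration B, on the 0–1 score, with the wrong diagnosis itself costing points.* Score = 0.5 × findings + 0.5 × (1 if the diagnosis is right, otherwise 0). True mix of radiculopathy, mononeuropathy, polyneuropathy and other: 25/30/20/25%. Findings scores: 0.7/0.8/0.6/0.9. Errors are either spread evenly over the other three labels or, in one arm, all go to polyneuropathy (true polyneuropathy errors remain spread).

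Worked case: 80% accuracy in both arms, AI-arm errors going to polyneuropathy, control errors spread. Mean score among reports labelled polyneuropathy:

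- Control: (0.0167 × 0.35 + 0.02 × 0.40 + 0.16 × 0.80 + 0.0167 × 0.45) / 0.2133 = 0.1493 / 0.2133 = 0.70
- AI arm: (0.05 × 0.35 + 0.06 × 0.40 + 0.16 × 0.80 + 0.05 × 0.45) / 0.32 = 0.192 / 0.32 = 0.60
- Difference: −0.10, although the true effect is 0

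| Accuracy, AI v control | Error pattern | True effect in each category | Apparent effect: radiculopathy, mononeuropathy, polyneuropathy |
|---|---|---|---|
| 80% v 80% | same in both arms | 0.00 | 0.00, 0.00, 0.00 |
| 80% v 80% | differs by arm | 0.00 | +0.058, +0.054, −0.100 |
| 90% v 80% | spread in both arms | +0.050 | +0.046, +0.044, +0.048 |
| 90% v 80% | differs by arm | +0.050 | +0.076, +0.072, −0.023 |

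A difference in accuracy alone distorts little. A difference in where the errors go can distort the effect materially and even reverse its sign.

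**3. Separate tests against a test of difference.** Two-sided 0.05, 80% power, standardised difference, n per arm: detectable d = 2.80 × √(2/n).

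- n = 100 (whole trial): 2.80 × √(2/100) = 0.40
- n = 33 (100 split evenly over three categories with no normal or other studies, an optimistic assumption): 0.69
- n = 25 (four equal groups): 0.79

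The difference between two category-specific effects has variance 4/n in place of 2/n. Its detectable size at n = 33 is therefore 0.69 × √2 = 0.98 SD. The question of where AI helps most is harder to answer than the separate tests make it look, so confidence intervals matter more here than p-values.

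**The case against.** The strongest reply is that this is a silence in an exploratory section. The protocol never says that the category is taken from the trial report. Its blinded accuracy ratings, sensitivity and specificity, and error log all imply some judgement of the right answer that could supply the label. An operational subgroup definition and an interaction model are often left to an SAP, which is not at hand, and planning separate analyses does not forbid an interaction test. The subgroups are run only if numbers allow, and section 5.2.1 already admits limited ability to detect small differences. Objective 4 does not name diagnostic categories and might be served by the error-pattern analysis. The normal v abnormal item speaks of AI performance and need not compare the arms.

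Most of this stands, and it limits the point to a conditional one. Two things remain. The method actually stated is a set of separate analyses by a label that arises after randomisation, and no arm-independent source is fixed. Nor do the exploratory label and the multiplicity correction remove selection on a post-randomisation variable.

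A reader might go further and infer that the subgroup effects are confounded by the arm. The documents do not support that. It would need report-based labels, which are not stated, and labelling that differs by arm, which is not known; the accurate term would in any case be conditioning on a post-randomisation variable. A reader might also cite the familywise error of three uncorrected tests, 1 − 0.95³ = 14.3%. That describes a plan without correction, whereas section 5.2.6 promises one.

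**Conclusion.** The point holds in conditional form, at low severity. The protocol does not fix where the diagnostic category comes from. If it comes from the scored report, the subgroups condition on an arm-dependent component of the outcome. The resulting bias is about 0.1 SD under illustration A and −0.10 to +0.06 on the 0–1 score under illustration B with no true effect. It is zero when accuracy and error pattern match between arms, and small when only accuracy differs. These sizes rest wholly on assumed case mixes and error patterns, and the protocol gives no reason to expect one pattern over another. That errors may differ in kind is at least something it plans to examine, through its comparison of AI and physician error types.

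The part about separate analyses does not depend on the source of the label: within-category tests do not test a difference in effect between categories. The primary comparison of the two arms is unaffected.

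**What to change.** In section 5.2.6, replace the separate analyses with one exploratory model for AIGERS containing arm, category and the arm-by-category interaction. Use a rank-based or bootstrap equivalent if the scores are as non-normal as sections 5.2.2 and 5.2.4 expect. Report the interaction test together with the category-specific differences and their confidence intervals.

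Define the category from the referral indication, extracted in the same way in both arms, and state that it is not taken from the report being scored. For normal v abnormal, likewise use a label from outside the scored report, for example a reading of the raw EDX data made blind to arm and without sight of the report. Such a reading could also supply diagnostic categories. The indication is the cleaner choice for these, because the arm is known before testing begins.

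The cost is modest. Patients enter by referral, so an indication should exist before randomisation. Section 3.3.2 lists it only as an AI input, however, without timing and without saying that it is captured for controls, so that needs confirming. The indication is coarser than the final diagnosis and answers a slightly different question: for which referrals AI helps, not for which diseases. A reference label for normal v abnormal may need an extra reading, which is best arranged before the reports are unblinded.
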